# Multiphase optimization implementation strategy for tobacco cessation interventions in primary care clinics: A cluster-randomized type 3 hybrid effectiveness-implementation trial

**DOI:** 10.18332/tid/217143

**Published:** 2026-03-24

**Keywords:** brief verbal intervention for smoking cessation (BISC), primary healthcare, clinicians, multiphase optimization strategy (MOST), factorial trial

## Abstract

**CLINICAL TRIAL REGISTRATION:**

The study is registered on the official website of Chinese Clinical Trials

**IDENTIFIER:**

ChiCTR2600115994

**ABBREVIATIONS:**

BISC: brief verbal intervention for smoking cessation, PHC: primary healthcare, CFIR: Consolidated Framework for Implementation Research, BWS: best-worst scaling, MOST: Multiphase Optimization Strategy, USP: unannounced standardized patient, PSU: primary sampling unit, SSU: secondary sampling unit, PPS: probability proportional to size, DSMB: Data and Safety Monitoring Board, IOF: Implementation Outcomes Framework, PSAT: Program Sustainability Assessment Tool, PRESS: Provider Report of Sustainment Scale, NPT: Normalization Process Theory, EBP: evidence-based practice

## INTRODUCTION

Tobacco use poses a significant public health threat in China, the world’s largest tobacco producer and consumer^1^. With over 1 million annual tobacco-related deaths, projected to reach 2 million by 2030, important action is needed^2^. The Healthy China 2030 initiative aims to reduce adult smoking rates from 27.7% in 2015 to 20% by 2030^3^, necessitating the implementation of evidence-based smoking cessation practices.

Brief verbal intervention for smoking cessation (BISC), a 1-3 minute verbal advice delivered by health professionals during routine consultations, is a highly effective^4^ and a cost-efficient approach^5^. Primary healthcare (PHC) providers are ideally positioned to deliver BISC^6,7^ due to their credibility^8,9^ and frequent contact with patients, particularly those with conditions like diabetes and hypertension, who could greatly benefit from smoking cessation^10^ and those who frequent PHC clinics.

Despite BISC’s effectiveness and an appropriate health workforce, its implementation in China has been insufficient^11,12^. Clinical data show that the percentage of clinicians who actively ask whether patients smoked is low, and only about one-third (33.9%) of patients report receiving such advice^13^. This demonstrates that BISC has not yet become a routine practice.

This challenge highlights a crucial gap in China’s research landscape, which has largely focused on developing new interventions rather than effectively implementing existing ones. To address this, our type 3 hybrid effectiveness-implementation trial will apply a rigorous and innovative methodology.

This study use of the Multiphase Optimization Strategy (MOST) framework to optimize a tobacco cessation implementation strategy, providing a novel paradigm for future public health research. The methodology and findings from this study are expected to be highly relevant and adaptable to other low- and middle-income countries (LMICs) facing similar public health challenges. The primary objective of this study is to identify the optimal set of implementation techniques for promoting BISC based on prior research on barriers and facilitators.

## METHODS

### Study design

*Hybrid and full factorial design*

This study is designed as a type 3 hybrid implementation trial^14^, concentrating on the development and assessment of the effectiveness of a specific implementation strategy to enhance the adoption and implementation of BISC. The design prioritizes the evaluation of implementation strategies while also examining clinical outcomes. The research adheres to the principles of the Multiphase Optimization Strategy (MOST)^15,16^ with its core component being a 2×2×2 full factorial design (Figure 1). This design will result in eight distinct experimental conditions and allows for the evaluation of the main effects and potential interaction effects of the implementation techniques, which is the core purpose of the optimization trial. The study has identified four key implementation techniques to be included in the trial. One of these, assessing readiness and identifying barriers and facilitators, will be included as a constant component in all eight conditions, ensuring a foundational level of support for all participants. The remaining three techniques serve as the three factors of the factorial design, each with two levels (present or absent) (Table 1).

**Table 1 T0001:** Full factorial design (2×2×2) with constant components within a type 3 hybrid effectiveness-implementation trial of BISC in primary healthcare facilities with a sample of 640 clinicians, Guangdong, China, January 2026 – December 2026

*Experiment* *conditions*	*Constant component*	*Optional components to be tested*		
	*Assess for readiness and* *identify barriers and* *facilitators*	*Identify and prepare* *champions*	*Alter incentive/allowance* *structures*	*Conduct educational* *meetings*
1	Yes			
2	Yes	Yes		
3	Yes	Yes	Yes	
4	Yes	Yes		Yes
5	Yes		Yes	
6	Yes		Yes	Yes
7	Yes			Yes
8	Yes	Yes	Yes	Yes

Yes: means included in intervention. No: means not included in intervention. The specifics form (such as ‘ranking primary healthcare clinicians’ execution of BISC and providing spiritual rewards for excellence’) of each component (such as ‘Alter incentive/allowance structures’) will be developed by inviting stakeholders to work together, following the principles of co-production. BISC: brief intervention for smoking cessation.

**Figure 1 F0001:**
[figure not shown]
Study design of the MOST-based type 3 hybrid implementation trial using a factorial design (2×2×2) in primary healthcare institutions with a total sample of 640 clinicians, Guangdong Province, China, January 2026 – December 2026

*Randomization*

Following multistage and clustered sampling, the allocation sequence will be generated using a random number table. Simple randomization for each group will be conducted independently by a statistician not affiliated with the research team. The randomization scheme will be sealed in an envelope and opened only at the time of formal randomization, enabling the researcher to execute the random assignment.

*Blinding*

Blinding will not be feasible for the researchers and study subjects (institutions and clinicians) as both groups will actively participate in implementing the assigned interventions based on their allocation status. To mitigate subjective analysis, outcome assessors and data analysts will be blinded. Upon completion of all unannounced standardized patient (USP) visits for clinicians and telephone callback for patients, the research team will disclose the participants’ allocated interventions. Institutions will be decoded before analysis, and the allocation status will not be revealed to the data analysts throughout the trial.

### Recruitment and informed consent

*Study setting*

The study will be conducted in primary healthcare institutions located in Guangdong Province, China, from January 2026 to December 2026. To ensure the generalizability of our findings across the diverse socioeconomic landscape of the country, we will strategically select institutions from three cities that represent a spectrum of economic development: a highly-developed city from the Pearl River Delta region, a moderately-developed city from either Eastern or Western Guangdong, and a less-developed city from Northern Guangdong. This deliberate selection allows us to rigorously test our implementation strategies under a wide range of conditions, from highly-resourced urban settings to more resource-constrained rural areas.

The selected institutions will include a variety of primary care settings, specifically community health service centers and township health centers/village health stations, to ensure a broad representation of primary care delivery models. We will recruit a sufficient number of institutions to meet the sample size requirements determined in the section sample size and power.

The institutional inclusion criteria are as follows: 1) the institution must have been a member of a compact medical consortium within the last three years; and 2) the institution must provide comprehensive primary healthcare services. The exclusion criteria for institutions include: 1) ongoing participation in any other smoking cessation intervention studies; and 2) ongoing participation in other implementation studies that are testing any of the specific implementation techniques used in our trial.

*Study population*

The study population is clinicians, encompassing licensed clinicians, licensed assistant clinicians, and certified village clinicians. Clinicians will be included based on the following criteria: 1) they have worked in a clinical capacity for at least six months; and 2) they provide outpatient and primary healthcare services. Conversely, clinicians will be excluded if they meet any of the following criteria: 1) they have previously received smoking cessation-related training or participated in a similar trial; 2) they are absent from work for one month or more; 3) they are a non-formal employee such as a temporary worker or rotational staff; and 4) they are currently participating in other studies related to any of the specific implementation techniques being tested in the present trial.

*Sampling procedure*

This study will use a multistage, clustered sample design. The primary sampling unit (PSU), which is a regrouped unit of clinics or facilities, will serve as the randomization unit. The sampling process will be conducted in multiple stages (Figure 2). The first stage involves the purposive selection of three cities within Guangdong province to ensure a comprehensive representation of different socioeconomic development levels. Specifically, we will select one highly-developed city from the Pearl River Delta region, one moderately-developed city from either Eastern or Western Guangdong, and one less-developed city from Northern Guangdong.

**Figure 2 F0002:**
[figure not shown]
Sampling procedure of primary healthcare facilities with 640 clinicians, Guangdong Province, China, January 2026 – December 2026

In the second stage, all primary healthcare institutions under the jurisdiction of the recruited local health authorities in these three cities will be included in the sampling frame. These institutions will then be regrouped into PSUs based on the number of clinicians. This ensures that each unit has a sufficient number of clinicians, preventing the exclusion of smaller institutions from the sampling process. The PSUs will then be sampled using a probability proportional to size (PPS) sampling method.

The study will be conducted as a cluster-randomized trial. The intervention will be delivered to the entire cluster (PSU), but the intervention’s effect will be measured at the clinician level. The measurement is based on the average performance of a random sample of clinicians within the cluster. This is achieved through unannounced standardized patient (USP) visits, which function as the final step of the sampling process. A minimum of 80 USP visits will be assigned to each experimental condition.

*Sample size and power*

Power analyses were conducted to determine the sample size needed to test the effect of the implementation strategies on our primary outcome, ‘clinician advice to quit’. The detailed definition and measurement of this outcome are provided in the section on study outcomes. Based on prior research, the baseline rate for this outcome was 33.9%^13^. Through stakeholder consultation, it was determined that a 40% increase in delivery, resulting in a final primary outcome of 47.46%, would be considered a clinically meaningful effect. Assuming a two-tailed test with an alpha level of 0.05 and a desired power of 0.8, a sample size of 28 participants per cluster is required. Accounting for the cluster-randomized design with a design effect (Deff) of 2 and adjusting for an anticipated 20% loss to follow-up, the sample size has been intentionally increased to further enhance statistical power for detecting higher-order interactions. Consequently, the required sample size for one experimental condition is approximately 80 participants. Given our study design with eight conditions (one condition per PSU, for a total of eight PSUs), this translates to 640 participants in total.

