### Optional components

*Incentives*

This strategy aims to enhance BISC implementation through a multi-pronged incentive approach, primarily targeting clinicians and organizational commitment.

*Foundational training*

Within the first week of the project intervention commencing, third-party experts will conduct a one-time training for all medical staff, focusing on BISC skills. This pre-implementation incentive aims to enhance the hospital’s overall knowledge and skills regarding BISC.

*Issue an administrative directive*

Hospital administrators and middle-level leaders (e.g. department heads) will issue a unified administrative directive within 24 hours of foundational training, mandating clinicians to actively perform BISC. This action aims to ensure low time-cost for clinicians.

*Assessment and public disclosure*

The execution of BISC will be incorporated into medical service quality assessments. Weekly, in conjunction with medical quality surveys, the Medical Affairs Department or a third party will conduct random patient follow-up checks to assess BISC implementation, and public the results.

*Identifying and preparing champions*

This strategy focuses on establishing internal champions within the institutions to drive BISC implementation. The timeline for this strategy will be extended to ensure effective engagement and training.

*Identification*

Recruitment calls will be issued to all hospital staff, offering research funding as an incentive to attract promoters. This should be conducted within one week of the project commencing.

*Selection and empowerment*

Following identification , one-on-one motivational interviews will be conducted with interested candidates to help them understand the role. After selection, formal promoters will be appointed based on these interviews and administrative assessments. This combined approach provides a balanced method for selecting capable and motivated individuals.

*Cultivation*

This is initiated immediately after empowerment and continues throughout the entire project cycle. Identified promoters will receive BISC-related learning materials and begin participating in practical projects with the project team. This will involve monthly participation opportunities in communication and training processes, and the promoters will begin organizing small-scale internal trainings within their departments. This aims to deepen their understanding and improve overall implementation efficiency.

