### Education and training

This strategy focuses on enhancing the knowledge and skills of all medical staff through structured educational activities. The frequency of these activities is designed to build momentum while avoiding an excessive burden on staff.

*Specialized workshops*

Starting from the first month, the project team will conduct periodic thematic workshops on BISC-related knowledge and lectures on execution for all hospital staff. These will be held monthly after the initial appointment of promoters. These will be held once a month.

*Embedded health education*

Starting from Week 1, it is imperative to reinforce the knowledge of tobacco control among healthcare professionals on a daily basis, utilizing a variety of concise formats to ensure effective dissemination of information.

*Training exchange*

Starting from Week 8, public health departments and department heads will organize periodic smallgroup salon activities and peer-sharing sessions for all hospital staff.

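### Randomization units are formed by clinician count, the only criterion stated, with nothing to keep organizationally linked facilities out of different conditions: an uncontrolled spillover risk

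*Protocol article*

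**What the plan says.** All references are to the Methods of the protocol article.

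- **Unit of randomization** (Sampling procedure): "The primary sampling unit (PSU), which is a regrouped unit of clinics or facilities, will serve as the randomization unit".
- **Frame and grouping** (Sampling procedure): "all primary healthcare institutions under the jurisdiction of the recruited local health authorities in these three cities will be included in the sampling frame". Then: "These institutions will then be regrouped into PSUs based on the number of clinicians". The reason given is size: "This ensures that each unit has a sufficient number of clinicians, preventing the exclusion of smaller institutions from the sampling process". The units are then drawn with probability proportional to size (PPS).
- **Number of units** (Sample size and power): "one condition per PSU, for a total of eight PSUs". The Randomization subsection describes simple randomization and mentions no restriction by city, health authority or consortium.
- **Eligibility** (Study setting): "the institution must have been a member of a compact medical consortium within the last three years". Community health service centers, township health centers and village health stations are all in scope.
- **Delivery of the techniques** (Optional components; Education and training): administrators and department heads "will issue a unified administrative directive within 24 hours of foundational training, mandating clinicians to actively perform BISC". Checks on delivery are made weekly and the results are made public. The call for champions goes to all staff. From week 8, "public health departments and department heads will organize periodic smallgroup salon activities and peer-sharing sessions for all hospital staff".

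The exclusions in Recruitment and informed consent cover participation in other studies, earlier cessation training, and temporary or rotating staff. Strengths and limitations does not mention contamination between conditions.

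**The concern.** A cluster design protects against contamination only as far as the cluster boundary follows the lines along which the intervention travels. Here the stated boundary follows headcount. The eligibility rule selects institutions with a recent organizational tie to other institutions, and the techniques consist of orders, published rankings and group activities, which are easily shared between linked facilities. A center and a station that reports to it could be grouped into different PSUs, or two sampled PSUs could contain members of the same consortium.

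The trial's purpose is to choose a set of techniques. The last paragraph of the Qualitative analysis section says that techniques with statistically significant positive main effects will be identified, with interactions examined for synergy or antagonism. Dilution could drop a useful technique, and a spurious interaction could mislead the choice of combination. With a single PSU per condition, there is no second PSU in the same cell to reveal or offset a contaminated one.

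**Working it through.** **1. The plan's own figure.** Sample size and power gives a baseline of 33.9% and a 40% relative increase: 33.9 × 1.40 = 47.46%. The planned difference is 47.46 − 33.9 = 13.56 points. No allowance for spillover is stated.

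**2. What the layout forces.**
- Eight PSUs in three cities: at least one city must hold three or more PSUs, since two per city gives only six. Those PSUs are all under different conditions.
- The eight conditions are all distinct, so any two PSUs differ in at least one factor. On a given factor, a given PSU differs from 4 of the other 7.

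**3. Dilution of a main effect (assumed exposure).** Let c be the share of clinicians at the absent level of a factor who are in effect exposed to it, averaged over all four absent PSUs, with the full effect in each exposed clinician. Observed difference = 13.56 × (1 − c). The sample size needed for the same power grows by about 1/(1 − c)², ignoring the small change in binomial variance.

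| Assumed exposure | Difference (points) | Sample size ratio |
|---|---|---|
| 10%, all four absent PSUs | 13.56 × 0.90 = 12.2 | 1.23 |
| 25%, all four absent PSUs | 13.56 × 0.75 = 10.2 | 1.78 |
| 40%, all four absent PSUs | 13.56 × 0.60 = 8.1 | 2.78 |
| 25%, one absent PSU only | 13.56 × (1 − 0.25/4) = 12.7 | 1.14 |

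The last row is the relevant one for a single linked pair, taking the four PSUs as equal in size.

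**4. Effect on interactions.** Take effects that are truly additive on the difference scale, and let the education technique reach 25% of clinicians in one absent PSU. That cell rises by 0.25 × 13.56 = 3.39 points. The education effect at that PSU's champion level, averaged over the two incentive levels, falls by 3.39/2 = 1.7 points, from 13.56 to about 11.9. At the other champion level it stays at 13.56.
- If the contaminated PSU is condition 1 (no optional technique), the education-by-champion interaction appears as +1.7 points.
- If it is condition 2 (champions only), it appears as −1.7 points.

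The true interaction is zero in both cases, so the sign depends on which cell is contaminated.

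**The case against.** The strongest reply is that this is a condensed article. The sampling scheme is also shown in Figure 2, which is not available here, and the full protocol may contain further grouping rules. That stands to this extent: headcount is the only criterion stated, which does not prove it is the only one used. But the article does more than stay silent. It fixes a rule and gives a reason for it, and the rule as written permits linked facilities to be separated.

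Second, the documents never describe the consortium as a route of delivery. It appears only in the eligibility list, and the techniques are described as acting within institutions. A reader might infer that the consortium itself issues the directives or runs the shared activities. The text does not support that, since it says nothing on consortium management, size or joint staff activities. Nor does it say that every institution belongs to one now; the criterion is membership within the last three years.

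Third, safeguards exist. Whole facilities are grouped, so spillover would have to run between facilities rather than within one, and the exclusion of rotating staff keeps some mobile clinicians out of the sample. Both reduce the risk, but neither addresses facilities linked by management.

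Fourth, the exposure rates are assumptions. A reader might attach the 10.2-point figure to one contaminated pair. That figure needs 25% exposure across all four absent PSUs; one affected PSU gives 12.7. A reader might also conclude that spillover pulls every effect towards zero, which step 4 shows is untrue of interactions. Nor can a probability be put on two PSUs sharing a consortium, because the number of consortia is not given.

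Finally, one PSU per condition already confounds condition with PSU, and preventing spillover does not cure that. This is correct, but it is a separate weakness and no reason to leave this one open.

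**Conclusion.** The point holds as an uncontrolled risk. The stated rule for forming and drawing PSUs allows organizationally linked facilities to receive different conditions, and nothing in the article prevents, limits or measures the resulting spillover. It does not hold as a finding that contamination will occur or has occurred.

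The size cannot be determined from the documents. Under the assumptions in the working, the loss runs from about 0.8 of a point (one absent PSU, 25% exposed) to about 5.4 points (all four absent PSUs, 40% exposed) of the planned 13.56. These figures are illustrative and should not be quoted as estimates. The conclusion itself rests only on the grouping rule, the eligibility criterion, the delivery routes and the allocation of one PSU per condition.

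**What to change.** In the Sampling procedure section:

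1. State that a township or community center and its subordinate stations stay in the same PSU.
2. Draw the eight PSUs so that, where the frame allows, no two share a consortium; on a repeat, take the next PSU on the PPS list. A whole consortium need not fit inside one PSU. That matters because a PSU is planned at about 640/8 = 80 clinicians and consortium size is unknown.
3. Add an item to the endline clinician questionnaire (Table 2 already schedules questionnaires then), asked in all eight conditions, on exposure to each technique's activities. Place it after the clinician's standardized-patient visit so that it does not alert the clinician.
4. Report any consortium overlap between PSUs by condition. Items 3 and 4 remain possible if the PSUs have already been drawn, as they may be, since the study period starts in January 2026.

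The cost is protocol wording, a check of the PSU list before the draw and one questionnaire item. The draw departs slightly from pure PPS, and PSU sizes become somewhat less equal.

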### Constant component

*Assessing readiness and identifying barriers and facilitators*

The strategy of assessing readiness and identifying barriers and facilitators will be included as a constant component across all eight experimental conditions. This ensures a baseline understanding of the implementation environment and addresses fundamental challenges uniformly across all participating sites.

A proactive assessment of the readiness of primary healthcare institutions and clinicians to implement BISC was conducted through an online questionnaire. This was completed within the first week of the project commencing. Conduct monthly online questionnaire and online focus group discussions to identifying contextual barriers and facilitators.

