Qualitative data analysis from stakeholders will be de-identified and imported into Nvivo 11.0 for transcription, organization, coding, and content analysis. Our qualitative data analysis will use a mixed approach, combining both deductive and inductive methods, to identify established themes, patterns, and new discoveries^28,29^. For the first phase of the study, data from our scoping review^30^ and stakeholder consultations were analyzed deductively using the Consolidated Framework for Implementation Research (CFIR)^31^ to identify barriers and facilitators. For the second phase, data from semi-structured interviews will be analyzed inductively to find new themes. These data will also be analyzed using NPT to evaluate how the BISC intervention is integrated and sustained in practice. To ensure our coding is reliable, two team members will independently code each interview, and any differences will be resolved through discussion.

The systematic decision-making process^32^, guided by data from the factorial trial, will be integral to this procedure. We will leverage the estimated main effects to identify techniques that have a statistically significant positive impact. We will also examine interaction effects to glean insights into potential synergies or antagonisms between the techniques. The final optimization of implementation strategies will be achieved by integrating information from both main and interaction effects, along with a consideration of the predetermined constraints of the optimization objective. This approach ensures that the final selection of techniques is the most effective and efficient combination.

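### The 80% power for 33.9% versus 47.46% is tied to no named contrast; for the main effects the trial uses, 640 clinicians give about 60-70% at those rates, and 28 per cluster does not follow from the inputs.

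*Protocol article*

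**What the plan says.** Under Sample size and power the protocol article takes clinician advice to quit as the outcome: "Based on prior research, the baseline rate for this outcome was 33.9"%. The Introduction shows that this figure describes current practice, since "only about one-third (33.9%) of patients report receiving such advice". The effect is defined once: "it was determined that a 40% increase in delivery, resulting in a final primary outcome of 47.46%, would be considered a clinically meaningful effect". The error rates follow: "Assuming a two-tailed test with an alpha level of 0.05 and a desired power of 0.8". From these the article obtains 28 participants per cluster. It then applies a design effect of 2 and 20% loss, and rounds up to about 80 per condition, with one primary sampling unit per condition and 640 clinicians in all. The powered comparison is described only as the effect of the implementation strategies, in the plural.

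Under Study design, "The remaining three techniques serve as the three factors of the factorial design, each with two levels (present or absent", and a fourth technique is constant in all eight conditions. The Constant component section says that it "addresses fundamental challenges uniformly across all participating sites". Data analysis specifies a log-link binomial GEE with effect coding, and the decision process begins: "We will leverage the estimated main effects to identify techniques that have a statistically significant positive impact". Interactions and predetermined constraints also enter the final choice.

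**The concern.** A power statement has meaning only for a named comparison. In this 2×2×2 design the candidates differ widely: a main effect (320 against 320 clinicians), one condition against another (80 against 80), or an interaction. The article states the rates and the power but attaches them to none of these. It also leaves open whether 47.46% is what one technique should achieve or what the whole package should achieve.

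With effect coding, a main effect compares the average of the four conditions where a technique is present with the average of the four where it is absent. The current-practice rate of 33.9% is the expected rate at the 'absent' level only if the other two techniques and the constant component all do nothing.

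Significant main effects are one stated input to choosing techniques. If their power is well below 80%, a useful technique may fail to reach significance, and a reader relying on the stated power would take that as stronger evidence against it than it is.

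**Working it through.** **Inputs.** From Sample size and power: p0 = 0.339, p1 = 0.339 × 1.4 = 0.4746 (difference 0.1356), two-sided alpha 0.05, power 0.8, design effect 2, loss 20%, 80 per condition. From Table 1: four conditions at each level of a factor, so 4 × 80 = 320 clinicians per level.

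**1. The plan's own figure.** For two proportions, with p̄ = 0.4068,

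n per level = [1.96·√(2p̄(1−p̄)) + 0.842·√(p0(1−p0)+p1(1−p1))]² / (p1−p0)² = (1.3616 + 0.5791)² / 0.1356² = 204.8, so 205.

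Variants give 202 (unpooled), 205 (arcsine) and 220 (continuity corrected). Over the four clusters at a factor level this is 205/4 ≈ 51 per cluster (220/4 = 55 with the correction), before design effect and loss. The stated 28 is not reproduced.

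Two routes do reach 28, but neither follows from the stated inputs. One divides the corrected per-level figure by all eight clusters (220/8 = 27.5). The other reads the 40% as percentage points (33.9% against 73.9%, continuity corrected: 28 per group). The later steps are consistent with 28: 28 × 2 / 0.8 = 70, raised to about 80.

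**2. Power of 640 clinicians for a main effect at the stated rates.** With m effective clinicians per level,

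z = [0.1356·√m − 1.3616] / √(p0(1−p0)+p1(1−p1)), with denominator 0.6881, and power = Φ(z).

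- 20% loss: m = 320 × 0.8 / 2 = 128; z = (1.5341 − 1.3616)/0.6881 = 0.251; power 60%.
- No loss: m = 320 / 2 = 160; z = (1.7152 − 1.3616)/0.6881 = 0.514; power 70%.
- The stated 28 per cluster: m = 4 × 28 = 112; z = 0.107; power 54%.
- One condition against another, 20% loss: m = 80 × 0.8 / 2 = 32; power 19%.

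**3. Who is in the comparator.** From Table 1, the 'absent' conditions are 1, 5, 6, 7 for champions; 1, 2, 4, 7 for incentives; and 1, 2, 3, 5 for educational meetings. Each set contains condition 1, two conditions with one other technique, and one condition with both others. All receive the constant component.

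**4. Does the mixed comparator change the power?** The article gives no effects for the other techniques, so these are assumptions. The constant component is taken as inert and interactions as absent. If each other technique has ratio r, the 'absent' mean is 0.339(1+r)²/4; if each adds e points, it is 33.9% + e.

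| Effect kept for the tested technique | Other two techniques, each | Absent mean | Present mean | Power, m = 128 |
|---|---|---|---|---|
| either scale | inert | 33.9% | 47.46% | 60% |
| ratio 1.4 | ratio 1.1 | 37.4% | 52.3% | 67% |
| ratio 1.4 | ratio 1.2 | 41.0% | 57.4% | 75% |
| ratio 1.4 | ratio 1.3 | 44.8% | 62.8% | 82% |
| ratio 1.4 | ratio 1.4 | 48.8% | 68.3% | 89% |
| +13.56 points | +5 points | 38.9% | 52.5% | 59% |
| +13.56 points | +10 points | 43.9% | 57.5% | 58% |
| +13.56 points | +13.56 points | 47.5% | 61.0% | 59% |

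The 60% arises before any other technique is assumed to work. A higher comparator leaves power almost unchanged on the absolute scale and raises it on the ratio scale, which is the scale of the log-link model.

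**The case against.** Sizing on a baseline rate and a minimum worthwhile effect, with nothing assumed about the other factors, is an ordinary simplification for a factorial trial. If the others are inert, the main effect is exactly 33.9% against 47.46%. If they work, step 4 shows the simplification to be neutral or conservative. A journal article may also leave eight expected condition rates to a fuller document. All of this stands, and it removes any claim that the mixed comparator is what costs the trial its power. It does not repair the mismatch between the stated inputs and the 28, or the missing name of the contrast, both of which lie in the text as printed.

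A reader might infer something stronger from the wording: that 47.46% is the full-package result, so each technique contributes only a part. An equal split (ratio 1.4^(1/3) = 1.119 each) would give 38.0% against 42.6% and 11% power (13% without loss). The article states no such split, and the low figure comes from the smaller difference of about 4.5 points, not from the comparator. A reader might also see a contradiction, because three ratios of 1.4 multiply to 33.9% × 1.4³ = 93.0%. The article, however, never claims both 40% per technique and 47.46% for the package, and it plans to look for antagonism between techniques. Nor are techniques chosen on significance alone, since interactions and constraints also count.

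**Conclusion.** The point holds as a defect in the power statement. The 80% is attached to no named contrast, and it is not met for a main effect at the stated rates: about 60% with 20% loss and 70% without. The stated 28 per cluster should be about 51 (55 with continuity correction). The 33.9% is the right comparator rate only if the other techniques and the constant component have no effect. Departing from that assumption gives 58-59% if the absolute difference is kept and 67-89% if the ratio is kept, so power passes 80% only when the ratio is kept and the other techniques are themselves strong (ratio about 1.3 or more each). The documents do not support saying that the mixed comparator causes the shortfall, or that single-technique power is 11-13%.

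These figures use a normal approximation and take the design effect of 2 as stated. With four clusters at each factor level they are optimistic, which is a separate matter.

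**What to change.** In Sample size and power:

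- Name the powered contrast as the main effect of one technique: the four conditions with it against the four without it.
- State that the 40% is per technique and whether it is held as a ratio or as an absolute difference. If it is instead the package target, say so and give the much lower single-technique power under a stated split.
- Say that 33.9% is a current-practice rate, which equals the comparator rate only if the other techniques and the constant component have no effect.
- Correct the 28 per cluster, or show the inputs that produce it.
- Restate the power of 640 clinicians for that main effect: about 60-70% at 33.9% against 47.46%, with a range over assumed effects of the other techniques.

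The cost is one rewritten paragraph and a short recalculation. Sites, clinicians and visits stay as planned. The downside is a less favourable stated power.
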